### Blinding

This is a double-blinded study design. All research personnel and study participants will be blinded throughout the trial. To ensure all investigators and research personnel remain blinded, the company producing the nutritional supplements and placebo will be responsible for providing the Pharmacy Research Support Services (PReSS) and information technology (IT) technician with the allocation information specific to each lot number. All prepackaged kits for preoperative intake and postoperative intake will be sent directly to PReSS. The kits received by PReSS will include a lot number that will correspond to either the intervention or placebo; however, as mentioned above, the only personnel aware of the lot numbers and associated randomization allocation will be the independent pharmacy lead, pharmacy technicians at PReSS, and the independent IT technician responsible for the randomization sequence. To ensure all research personnel remain blinded to the patients’ allocation, PReSS will remove the lot number from each kit. PReSS will also be responsible for the accountability of the supplements throughout the study.

After entering the patient information into the Interactive Registration and Randomization System, PReSS will be responsible for dispensing the appropriate kit number and ensuring the lot number has been blinded from the patient and the research personnel. The individual packets within the kits will be labeled from “30 days before surgery” to “5 days after surgery.”

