#### Protein Isolate Powder (ISOlution)

This will be consumed by the patient to increase muscle protein synthesis and achieve the recommended per meal protein intake prior to surgery as well as after surgery. Each serving delivers 20 g of protein stirred into a minimum of 250 mL of liquid or soft foods. Patients will be asked to consume 1 serving per day (20 g of protein powder in total per day) from the time of randomization up to 6 days before surgery (up to 30 days in total).

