#### Immunomodulation-Formulated Liquid Diet (INergy-FLD)

In preparation for surgery, patients will consume an immune-modulating formula containing various ingredients, including arginine, protein isolate, omega-6 fatty acids, and RNA, aimed to attenuate excessive inflammatory responses without being immunosuppressive and to replenish nutrients that are depleted in a state of stress (ie, surgery), thereby enhancing the recovery process [1]. The volume of this solution is 250 mL per dose (51 g of powder reconstituted in 250 mL of cold water). Patients will be asked to consume 3 doses per day for 5 days prior to surgery and 5 days following surgery.

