### Administration

Following randomization, patients will receive blinded packages of either the intervention or the placebo, which will be administered by the PReSS, located in the A4 wing at JHCC. The patients will be responsible for administering their own supplements while at home.

Patients will be asked to consume 1 serving of 20 g of protein isolate powder mixed in 250 mL of liquid or soft foods every day from the date of randomization to up to 6 days before surgery. Additionally, they will be asked to consume 3 servings of 51 g of an immune-modulating formula mixed in 250 mL of cold water for 5 days before and after surgery as well as 2 servings of 55 g of carbohydrate-rich powder mixed in 400 mL of cold water the evening before surgery and 1 serving 2-3 hours before anesthesia. Administration of the carbohydrate loading substance will be modified for patients following the Enhanced Recovery After Surgery (ERAS) Protocol. All study participants who are also taking part in the ERAS Protocol will be asked not to take the carbohydrate loading supplement as per the ERAS Protocol and will be asked to take the carbohydrate loading substance (or placebo) provided for this study. Routinely at our center, patients undergoing colorectal surgery are enrolled in an ERAS Protocol that encourages drinking fluids on postoperative day 1. Patients undergoing hepatobiliary surgery (either pancreas or liver surgery) are not included in an ERAS pathway; however, they are also encouraged to start a diet usually composed of liquids on day 1 after surgery. Patients undergoing gastric surgery are kept nothing per mouth for 7 days. However, they are started on tube feeds on day 1 after surgery.

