At this point, patients will fill out a daily compliance diary from the date of randomization until up to 5 days after surgery. This compliance diary will be transcribed into a preoperative compliance case report form (CRF) that includes the number of packets the patient took every day, the volume that was ingested, the days it was ingested for, and the reasons patients were not compliant. While in the hospital, the nurses will be responsible for administration, as PReSS will facilitate the administration of the supplements (INergy-FLD) by adding them to the nursing care pathway of the patients. Compliance during this time will be obtained from the nurses’ log, which includes the amount of solution the patient ingested during each administration and the days the patient ingested the solution. If for some reason, the patients are unable to tolerate an oral diet (postoperative complications such as delayed gastric emptying, ileus or bowel obstruction, etc), the nurse will contact the principal investigator of the study and the order to suspend the administration of the solution will be assessed for each patient. This will be noted in the nurses’ chart and transcribed to the postoperative compliance CRF. Patients will continue to be part of the study.

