### Statistical Analysis

Patient baseline characteristics and demographics by treatment group will be presented using descriptive statistics. The proportion of eligible patients randomized and its corresponding 95% CI will be calculated using the Wilson method. The criterion for success of this study is defined as the proportion of eligible patients randomized as ≥60.0% (60/100). If the estimated proportion is <40.0% (40/100), the trial will be considered not feasible. If the proportion is between 40.0% (40/100) and 59.0% (59/100), the trial will be considered feasible, with modifications to improve enrollment.

The difference in the proportions of any postoperative complication between groups and its corresponding 95% CI will be calculated using the Wilson method. The proportion of patients who are compliant with study therapy and 95% CI will also be calculated. Differences in compliance between treatment groups will be described. Good compliance will be defined as consumption of ≥70% (at least 41/58) sachets of the study intervention before and after surgery. If the compliance is ≥70% (at least 41/58 sachets), there will be no exploratory analysis to evaluate the reasons for noncompliance. Compliance of <70% (40/58 sachets or less) will be considered poor, and reasons for noncompliance will be further explored (eg, problems with the distribution or administration of the supplements, bad taste, side effects, inability to tolerate oral intake, etc) These reasons will be clearly stated in the compliance CRFs.

The mean (SD) of the CCI at 90 days from the index surgery will be estimated for each group, and the mean difference between groups will be estimated with its corresponding 95% CI. QoL scores will be summarized using means and corresponding SDs. The mean difference in the QoL scores between groups at 1 and 3 months will be estimated using linear models adjusting for baseline QoL scores.

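### The pooled 41/58 compliance cut can class a patient with no postoperative intake as good and then rules out the analysis of reasons

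*Protocol article*

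**What the plan says.** The Statistical Analysis section sets one threshold over both periods: "Good compliance will be defined as consumption of ≥70% (at least 41/58) sachets of the study intervention before and after surgery". What follows depends on which side of it compliance falls. Above it: "If the compliance is ≥70% (at least 41/58 sachets), there will be no exploratory analysis to evaluate the reasons for noncompliance". Below it: "Compliance of <70% (40/58 sachets or less) will be considered poor, and reasons for noncompliance will be further explored". Inability to tolerate oral intake is among the examples of reasons to be explored, but only on the lower side.

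Secondary Outcomes repeats the 41/58 definition. It also says that compliance will be weighed when feasibility is judged, because poor compliance might call for protocol changes. The first secondary objective is the proportion of enrolled patients who complete the perioperative program, and it refers to that definition.

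Only the immunomodulating formula is given after surgery: "Patients will be asked to consume 3 doses per day for 5 days prior to surgery and 5 days following surgery". The Administration section provides for patients who cannot tolerate an oral diet after surgery, naming delayed gastric emptying, ileus and bowel obstruction. In that case "the order to suspend the administration of the solution will be assessed for each patient", and the patient stays in the study.

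**The concern.** The program is perioperative, and one of its two phases contributes only about a quarter of the sachets. A cut of 70% on the pooled count can then be met from the preoperative phase alone. The postoperative phase, where the protocol foresees intolerance and suspension, need not contribute anything.

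The switch-off sentence makes this worse. Once the pooled cut is met, the plan excludes the analysis that would show why postoperative sachets were not taken. The team planning the larger trial could read a favourable compliance figure without seeing that one component had been poorly delivered.

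**Working it through.** **Inputs**

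- Protein isolate, all preoperative: one serving a day, "from the time of randomization up to 6 days before surgery (up to 30 days in total"). The Blinding section says the packets "will be labeled from “30 days before surgery” to “5 days after surgery". Days -30 to -6 inclusive are 25 servings.
- Immunomodulating formula: 3 × 5 = 15 before surgery and 3 × 5 = 15 after.
- Carbohydrate, all preoperative: 2 + 1 = 3.
- Wait: surgery should take place within 4 weeks of enrollment (Nutritional Supplements and Placebo), that is 28 days.

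**Reproducing the plan's figures**

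25 + 15 + 3 + 15 = 58, as stated. The cut is 0.70 × 58 = 40.6, rounded up to 41; 41/58 = 70.7% and 40/58 = 69.0%. These agree with the text. Counting 30 protein servings would give 63, so the stated 58 rests on 25.

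**Split by phase**

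Preoperative: 25 + 15 + 3 = 43, or 43/58 = 74.1% of the total. Postoperative: 15, or 15/58 = 25.9%. Full preoperative intake with 0 of 15 afterwards gives 43/58 = 74.1%, classed as good. Up to 43 − 41 = 2 preoperative sachets could also be missed.

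**Dependence on the wait**

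Let surgery fall D days after randomization, with the first protein serving on the day of randomization. Then protein = D − 5, preoperative sachets = D + 13 and total prescribed = D + 28. With full preoperative and no postoperative intake:

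| D (days) | Preoperative | Prescribed | Share of prescribed | Share ≥70%? | Count ≥41? |
|---|---|---|---|---|---|
| 21 | 34 | 49 | 69.4% | no | no |
| 22 | 35 | 50 | 70.0% | yes | no |
| 27 | 40 | 55 | 72.7% | yes | no |
| 28 | 41 | 56 | 73.2% | yes | yes |
| 30 | 43 | 58 | 74.1% | yes | yes |

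If compliance is a share of what was prescribed, the condition is (D + 13)/(D + 28) ≥ 0.70, which solves to D ≥ 22. If the count of 41 is fixed, it is D + 13 ≥ 41, so D ≥ 28; at 28 days the patient scores 41/58 = 70.7% and has no sachet to spare.

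**By volume**

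Secondary Outcomes also speaks of percentage volume. Taking 250 mL per protein serving (stated as a minimum), 250 mL per immunomodulating dose and 400 mL per carbohydrate dose:

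- Preoperative: 25 × 250 + 15 × 250 + 3 × 400 = 11,200 mL.
- Total: 11,200 + 15 × 250 = 14,950 mL.
- Share: 11,200/14,950 = 74.9%.

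The break-even wait is 21 days (8,950/12,700 = 70.5%). The result is much the same.

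**By product**

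Missing all three carbohydrate servings and nothing else gives 55/58 = 94.8%.

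**The case against.** The strongest reply is that the gap is narrow. The 74.1% case needs a start at day -30, while surgery is meant to occur within 4 weeks. With the count of 41 applied as printed, a patient with no postoperative intake passes inside that window only on its last day, and then only with 41 of 41 preoperative sachets. At 27 days the same patient has 40, is classed as poor, and the reasons are explored. This stands and limits how often the problem can arise. It does not remove it: on the share-of-prescribed reading the range runs from 22 days, and the article does not say which reading applies to patients prescribed fewer than 58.

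Second, nothing is lost from the data. Nurses log postoperative intake, there is a specific form for postoperative volume, and reasons and suspensions go on the compliance forms. This stands too: the failure is excluded from the planned analysis, not from the record.

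Third, tables by phase may well be in a statistical analysis plan that is not shown. That is fair as to the tables. It does not cover the sentence ruling out the analysis of reasons, which the article states outright.

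Fourth, the formal stop, modify or continue rule rests on the proportion randomized. Compliance only informs the judgement, so the consequence for the larger trial is indirect.

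A reader might also take "Patients undergoing gastric surgery are kept nothing per mouth for 7 days" as a sign that the postoperative component cannot be delivered. It does not show that: the next sentence in Administration says these patients start tube feeds on day 1, and Feeding Tube Administration allows the immunomodulating formula by tube.

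**Conclusion.** The point holds as a minor one. A single pooled cut with 43 of 58 sachets before surgery can class a patient with 0 of 15 postoperative sachets as having good compliance, and the plan then drops the analysis of reasons. The size is 74.1% on the full schedule and 70.7% (of 58) or 73.2% (of 56) with surgery at 28 days. It rests on complete or near-complete preoperative intake and on a wait of about 22 days or more (share of prescribed) or 28 days or more (fixed count).

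The article does not say whether the 70% trigger works per patient or for the trial as a whole. Pooling can mask the postoperative phase either way.

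Two stronger readings are tempting, and the document supports neither. One is that the whole cohort could be reported as compliant with no postoperative intake at all. That would need every patient to wait long enough and take nearly all preoperative sachets; the article gives no distribution of waits, and 4 weeks is an upper limit. The other is that postoperative non-delivery is the likeliest failure. The article gives no rate of intolerance or suspension and describes it only as a contingency.

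**What to change.** - Keep the pooled figure as defined, and state whether its denominator is 58 or the number prescribed to that patient.
- Report percent of prescribed intake separately for the preoperative and postoperative phases, and by product, with 95% CIs.
- Delete the sentence that rules out analysis of reasons when the pooled cut is met.
- Tabulate the recorded reasons, with study-ordered suspensions shown as their own category, for any shortfall below 70% in either phase, whatever the pooled figure. On the full schedule that means fewer than 31 of 43 before surgery (0.70 × 43 = 30.1) or fewer than 11 of 15 after (0.70 × 15 = 10.5).

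These phase cuts only prompt a table of reasons. Redefining a compliant patient as one with at least 70% in each phase is not needed; it would be a debatable choice, since it would label patients noncompliant when the study itself suspended their doses.

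Separately, the 30 days of protein stated in the abstract, the 4-week limit to surgery and the 25 protein days implied by 58 sachets do not agree and should be reconciled.

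The cost is slightly more tabulation and a possibly less favourable picture of compliance. Separate preoperative and postoperative compliance forms already exist, so no new data collection is needed.

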Liver resection: ~60% (~50/80) are performed laparoscopically.Pancreaticoduodenectomy: all are performed open; there is no routine placement of feeding jejunostomy; ~70% (~50/70) are performed with the classic approach, while the rest are performed preserving the pylorus.Distal pancreatectomies: ~80% (~16/20) are performed laparoscopically, either spleen-preserving or not, depending on tumor location.Rectal resection: routine total mesorectal excision, ~30% (~10/30) are performed laparoscopically.Colon resections: high ligation of the colic vessels, ~40% (~30/70) are laparoscopic.Gastrectomy: all are performed open with a modified D2 lymphadenectomy (no splenectomy).

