### Stratification

Stratification will be employed prior to enrollment to ensure a balance between treatment arms for a factor that may influence the primary outcome, including the nutritional status of the patient. Prior to randomization, patients’ overall risk of malnutrition will be determined using the Malnutrition Universal Screening Tool (MUST) [29]. Patients will be stratified by risk status as low risk of malnutrition (MUST score of 0) versus medium and high risk of malnutrition (MUST score of 1 or 2).

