### Sample Size and Feasibility

Currently, there are 200 gastrointestinal resections performed annually for gastrointestinal cancer at JHCC (300 over an 18-month period). We expect at least 55.0% (165/300) patients to be eligible for the study. Additionally, we expect that 60.6% (100/165) eligible patients will be randomized to either intervention or placebo. Assuming a two-sided alpha of .05, this will give us a 95% CI around the estimate of 53.0%-68.0%. A sample size of 100 (50 per group) will enable us to estimate the treatment effect and corresponding variance of the complication rate, CCI, and QoL measures with adequate precision. Given the number of patients that undergo surgery at JHCC and the number of patients eligible for the study, we believe we can complete accrual to the study in 18-21 months. Given that the follow-up is 3 months, we expect the study to be finalized within 21-24 months of commencement.

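### The stated complication and CCI differences are crude: they leave out the MUST stratum and the planned procedure, both known before randomization; the estimates are valid, and adjusting for a few broad groups would cost little

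*Protocol article*

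**What the plan says.** All references are to the protocol article.

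- **Complications** (Statistical Analysis): "The difference in the proportions of any postoperative complication between groups and its corresponding 95% CI will be calculated using the Wilson method". No covariate or stratum is named.
- **CCI** (Statistical Analysis): after group means and SDs, "the mean difference between groups will be estimated with its corresponding 95% CI". Again no covariate is named.
- **QoL** (same paragraph as CCI): the group difference "will be estimated using linear models adjusting for baseline QoL scores".
- **Randomization** (Stratification): "Patients will be stratified by risk status as low risk of malnutrition (MUST score of 0) versus medium and high risk of malnutrition". The section gives as its reason that nutritional status may influence outcome. Procedure is not a stratum.
- **Case mix** (Recruitment): for liver resection about "60% (~50/80) are performed laparoscopically"; "Pancreaticoduodenectomy: all are performed open"; gastrectomy is also always open, and about 40% of colon resections are laparoscopic.
- **Pathways** (Administration): colorectal patients follow ERAS and hepatobiliary patients do not. "Patients undergoing gastric surgery are kept nothing per mouth for 7 days", with tube feeding from day 1.
- **Purpose** (Sample Size and Feasibility): "A sample size of 100 (50 per group) will enable us to estimate the treatment effect and corresponding variance". The outcomes meant are complications, CCI and QoL.

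Eligibility requires an elective operation, and patients are found by screening those already scheduled for surgery. It follows that the planned procedure is known before randomization.

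**The concern.** The section is not silent on these outcomes. It fixes how both differences are computed, and both are crude. Two pre-randomization variables are left unused.

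The first is the MUST stratum. If it is prognostic, as the plan supposes, a crude interval after stratified randomization is wider than it need be.

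The second is the planned procedure, which neither the randomization nor the analysis takes into account. With 50 per arm, a moderate excess of one operation in one arm is an ordinary event, and whatever extra risk that operation carries then sits in the observed difference. These estimates and their variances are meant to inform a larger trial. If imbalance appears and no adjusted analysis has been named, any adjustment will look post hoc.

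**Working it through.** **1. The plan's own precision figure.** The only one that can be checked is the interval for 100/165 = 60.6%. Wilson gives 53.0% to 67.7% and Wald 53.2% to 68.1%. Both round to the stated 53% to 68%, so it reproduces. No precision is stated for complications or CCI.

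**2. Crude complication difference.** At 25/50 in each arm the Wilson limits are 0.366 and 0.634, a distance of 0.134 from 0.5. The Wilson-based (Newcombe) half-width for the difference is √2 × 0.134 = 0.189, or about 19 points. At 20/50 or 30/50 per arm it is also about 19 points. The crude SE is √(2 × 0.25/50) = 0.10.

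**3. Chance imbalance.** The Recruitment denominators are liver 80, pancreaticoduodenectomy 70, distal pancreatectomy 20, rectal 30 and colon 70, in total 270. Gastrectomy has no count. Pancreaticoduodenectomy is 70/270 = 25.9%.

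| Model | Share differs by ≥10 points | by ≥15 points |
|---|---|---|
| Two independent binomials (50, 0.259) | 0.30 | 0.09 |
| Exactly 26 of 100, randomly split 50:50 | 0.25 | 0.11 |

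**4. Cost and gain of adjusting CCI.** The approximate variance ratio of adjusted to crude is (1 − R²)(N − 3)/(N − 3 − k), with N = 100, k added terms and R² the share of variance they explain. The interval-width ratio is its square root times t(0.975, 98 − k)/t(0.975, 98).

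| k | Terms | R² = 0 | 5% | 10% | 20% | Break-even R² |
|---|---|---|---|---|---|---|
| 1 | MUST only | 1.005 | 0.980 | 0.954 | 0.899 | about 1% |
| 3 | MUST + three procedure groups | 1.016 | 0.991 | 0.964 | 0.909 | about 3% |
| 4 | MUST + four procedure groups | 1.022 | 0.996 | 0.969 | 0.914 | about 4% |
| 5 | Six procedures, no MUST | 1.028 | 1.002 | 0.975 | 0.919 | about 5% |

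All R² values are assumptions; the article gives none.

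**5. Does the grouping matter?** The article gives no complication rate by procedure, so I assume two sets, in the order liver, pancreaticoduodenectomy, distal pancreatectomy, rectal, colon, gastrectomy. Gastrectomy is given an assumed weight of 15 beside the 270, about 5%. R² is the between-group variance divided by p(1 − p), with p the overall rate.

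- *Narrow set* (40, 60, 45, 55, 40, 60%): p = 136.5/285 = 0.479. All six procedures give R² = 3.3%. For pancreatic (51/90 = 0.567), liver (0.40), colorectal (44.5/100 = 0.445) and gastric (0.60), the between-group variance is 0.00536 and R² = 0.00536/0.2496 = 2.1%. If pancreatic and liver are pooled as hepatobiliary, R² is 0.5%.
- *Wide set* (30, 70, 45, 55, 30, 70%): p = 130/285 = 0.456. All six give 12.7%. The four groups (0.644, 0.30, 0.375, 0.70) give 0.0235/0.2481 = 9.5%. Pooled hepatobiliary gives 2.4%.

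Keeping pancreatic and liver apart retains most of the between-procedure variance; pooling them loses most of it.

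**6. Size relative to the noise.** Imbalance in procedure contributes an SD of about √R² × SE to the crude difference: √0.033 × 10 = 1.8 points (narrow) or √0.127 × 10 = 3.6 points (wide), inside a crude SE of about 10 points.

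**7. Sparse cells.** In simulations of 100 patients with six separate procedures, 17% to 19% of trials had a procedure present in only one arm. In 18% to 27%, some procedure had complications in all or none of its patients. This argues for few groups and against a logistic model.

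**The case against.** The strongest reply is that nothing here is wrong. Randomization makes the crude estimates unbiased, and their standard errors already allow for chance imbalance. The outcomes are secondary and for estimation only, and the stop/modify/continue rule rests on the proportion randomized. Crude means and SDs are convenient inputs for planning a later trial. Covariate sets often sit in a statistical analysis plan, and the article does not exclude adjusted analyses. Adjusting QoL but not CCI is no contradiction, because QoL has a baseline score and the CCI has none. The procedure counts are rough: they have no time base, total 270 against 200 resections a year, omit gastrectomy and describe the center rather than eligible patients.

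All of that stands, and it limits the point to a minor one. It does not remove it, because the article does fix the two analyses and in doing so omits the factor it randomizes by.

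A reader might also infer that adjusting is free. It is not: the interval widens slightly if the factors are not prognostic, and under the narrow rates assumed above the procedure groups explain only 2.1% of the variance in complications, too little to pay for themselves. Nor does any broad grouping remove the imbalance. A hepatobiliary group would combine all-open pancreaticoduodenectomy with mostly laparoscopic liver resection. Even a pancreatic group still mixes pancreaticoduodenectomy with distal pancreatectomy.

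**Conclusion.** The point holds as a low-severity improvement. The planned complication and CCI differences ignore the MUST stratum and the planned procedure, and at 50 per arm a pancreaticoduodenectomy imbalance of 10 points or more has probability about 0.30 on the article's counts.

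It would be going too far to call the crude analysis biased or its intervals invalid, or to say that procedure must become a stratification factor; the article supports none of these. A guaranteed gain in precision cannot be claimed either. With 3 to 4 degrees of freedom the CCI interval is about 2% wider at worst. It becomes narrower only above roughly 3% to 4% explained variance, by about 3% to 4% at an assumed R² of 10% and about 9% at 20%. The firmer benefit is that an adjusted estimate is named in advance, so a visible imbalance need not prompt a post hoc choice. The feasibility decision is unaffected.

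**What to change.** In Statistical Analysis:

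- Estimate the CCI difference from a linear model with treatment, MUST stratum and planned procedure group.
- Use the planned procedure, not the one performed, so that the variable is fixed before randomization.
- Use a few broad groups that separate pancreatic from liver resection, for example pancreatic, liver, colorectal and gastric/other, with a rule for merging sparse groups set before unblinding.
- Give the complication risk difference Mantel-Haenszel weighted or standardized over the same factors. This keeps the risk difference as the estimand and avoids the separation and changed effect measure of a logistic model.
- Report the stated crude estimates alongside.

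Randomization and sample size stay as they are. The cost is analysis wording and 3 to 4 degrees of freedom. The scheduled operation should already be on record for every patient; it needs only to be captured as planned at randomization.

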For patients with gastrointestinal cancer, insufficient protein intake, insulin resistance, and postoperative immobility increase the risk of impaired immune function [19]. Insufficient protein intake also results in slower recovery, prolonging hospital stay and immobility [19]. Nutritional depletion is a major determinant of the development of postoperative complications. It is associated with changes in body composition, tissue wasting, and impaired organ function, which lead to impaired immune and muscle function. Thus, nutritionally depleted patients are at higher risk of infectious complications, and a direct relationship with increased operative mortality independent of the type of surgery has been observed [20]. Patients with gastrointestinal cancers typically experience malnutrition, significant weight loss, and reduced food intake. Thus, optimizing nutritional status both before and after surgery by meeting protein requirements creates an opportunity to reduce patients’ postoperative complications [21]. Whey protein substrates have great potential to be used effectively to support postsurgery anabolism. Whey proteins of high quality have proved to be effective in modulating muscle protein synthesis and are a convenient way to supplement protein needs in malnourished patients [22]. Whey proteins also have immunomodulating properties, including biosynthesis of the antioxidant glutathione, which could attenuate the catabolic effects of surgery and spare protein [23]. Albumin, muscle function tests, immunological status, and weight loss have been used to show the correlation between nutrition depletion and postoperative morbidity and mortality.

It has been proposed that perioperative immunomodulation, carbohydrate loading, and increased protein intake may have the potential to decrease overall complications, improve patients’ quality of life (QoL), improve disease-free and overall survival, and reduce overall health care cost by decreasing the length of hospital stay and readmissions [24,25].

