### Randomization

Randomization will be conducted centrally by the Ontario Clinical Oncology Group (OCOG). Study participants will be identified by screening all patients scheduled for surgery at JHCC. Eligibility must be confirmed by the treating physician or designated prior to enrollment. After confirmation and documentation of written informed consent, patients will be randomized by accessing OCOG’s Web-based Interactive Registration and Randomization System. Randomization will be performed according to a prescribed computer-generated schedule.

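### Randomization is stratified by malnutrition risk, but no planned between-group estimate uses the stratum, so secondary intervals can be somewhat wider than necessary

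*Protocol article*

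**What the plan says.** The Stratification section of the protocol article sets one factor with two levels: "Patients will be stratified by risk status as low risk of malnutrition (MUST score of 0) versus medium and high risk of malnutrition", the latter being a score of 1 or 2. The reason given is "to ensure a balance between treatment arms for a factor that may influence the primary outcome, including the nutritional status of the patient". The Introduction says that "nutritionally depleted patients are at higher risk of infectious complications" and presents depletion as one of the main drivers of postoperative complications generally.

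The Statistical Analysis section then fixes three between-group estimates:

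- Complications: "The difference in the proportions of any postoperative complication between groups and its corresponding 95% CI will be calculated using the Wilson method".
- CCI at 90 days: a mean and SD per group, and a mean difference with a 95% CI. No covariate is named.
- QoL: "The mean difference in the QoL scores between groups at 1 and 3 months will be estimated using linear models adjusting for baseline QoL scores".

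The MUST stratum appears in none of them. Compliance differences are only to be described. The primary outcome, the proportion of eligible patients randomized, involves no comparison of arms.

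**The concern.** A factor is normally stratified on because it is thought to predict outcome, and an analysis that then leaves it out forgoes part of the benefit. Variation between strata stays in the standard error. If the schedule balances the arms within strata, that standard error is larger than the true sampling variation of the estimate. If it does not, any chance imbalance on MUST stays in the estimate.

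Here the stratum can help only the secondary comparisons. Although the Stratification section speaks of the primary outcome, that outcome is being randomized, and balance between arms cannot affect it. The secondary comparisons matter for what follows: the Sample Size and Feasibility section says that "A sample size of 100 (50 per group) will enable us to estimate the treatment effect and corresponding variance" of complications, CCI and QoL with adequate precision, and the Introduction says the results will inform a larger trial.

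**Working it through.** **Inputs from the protocol article.** 50 patients per group; two-sided alpha 0.05; background morbidity 40% to 60% (Introduction), from which I take the midpoint, 50%. The article gives no MUST prevalence, no outcome rate by MUST level and no correlation of MUST with CCI or QoL. These are assumed below over a range.

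**The plan's own figure.** The only precision figure given is 53.0% to 68.0% around 100/165. The Wilson interval is 53.0% to 67.7% and the simple normal-approximation interval 53.2% to 68.1%. Both round to 53% to 68%, so it reproduces. It concerns the primary outcome; no precision is stated for any between-group estimate.

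**Complications.** Unstratified, SE = √(2 × 0.25/50) = 0.100, so the half-width is 1.96 × 0.100 = 19.6 points. (The Newcombe interval, built from Wilson limits, gives ±18.9 points at 25/50 versus 25/50.) With equal strata whose rates differ by d, the within-stratum variance is 0.25 − d²/4:

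| Gap d | Within-stratum variance | Stratified half-width | Narrower with stratum | Unstratified wider by |
|---|---|---|---|---|
| 10 points | 0.2475 | 19.5 points | 0.5% | 0.5% |
| 20 points | 0.2400 | 19.2 points | 2.0% | 2.1% |
| 30 points | 0.2275 | 18.7 points | 4.6% | 4.8% |
| 40 points | 0.2100 | 18.0 points | 8.3% | 9.1% |

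The variance falls by 4%, 9% and 16% at gaps of 20, 30 and 40 points, equivalent to about 4, 9 and 16 of the 100 patients. If only 30% are in the higher-risk stratum, the narrowing at those gaps is 1.7%, 3.9% and 7.0%.

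**CCI.** Unadjusted half-width = 1.96 × √(2/50) = 0.392 SD. Adjusting for a stratum with correlation ρ multiplies this by √(1 − ρ²):

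- ρ = 0.2: 0.384 SD (2.0% narrower)
- ρ = 0.3: 0.374 SD (4.6% narrower)
- ρ = 0.4: 0.359 SD (8.3% narrower)

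**QoL.** The model already contains baseline QoL. Let b be the correlation of baseline QoL with outcome, m that of MUST with outcome, and c that of MUST with baseline QoL. With both terms, R² = (b² + m² − 2bmc)/(1 − c²), and the further width ratio is √[(1 − R²)/(1 − b²)]. With b = 0.4 or 0.6 and c = 0.2 or 0.4, the further narrowing is:

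- m = 0.2: 0.1% to 0.9%
- m = 0.3: 0.3% to 3.1%
- m = 0.4: 2.4% to 6.6%

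Each range lies below the CCI gain at the same correlation.

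**Coverage by simulation** (n = 100, 6,000 runs, equal strata, no treatment effect). With blocks of 4 within strata, the unstratified complication interval covers 94.3%, 95.3% and 96.4% at gaps of 20, 30 and 40 points. The unadjusted mean-difference interval covers 95.5%, 95.7% and 96.5% at ρ = 0.2, 0.3 and 0.4, against about 95% when adjusted. With simple randomization the unadjusted intervals stay at about 95%, while adjusting still narrows the mean-difference interval, for example from an average width of 0.796 to 0.764 SD at ρ = 0.3. With a non-prognostic stratum there is no gain: average widths are 0.791 unadjusted and adjusted under blocking, and 0.796 and 0.800 under simple randomization.

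**The case against.** The strongest reply is that the loss is conditional and small. It requires MUST to predict the outcome, and the article supports that only qualitatively, for complications and not for QoL. At a 20-point gap the half-width changes from 19.6 to 19.2 points, which would not alter a phase III decision. This stands and limits the weight of the point.

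A second reply is that covariates are analysis-plan detail, and the analysis plan is not shown. This stands in part: the complication and CCI sentences never say unadjusted. But the section does choose a method for complications and does name the QoL covariate, so an analysis plan that added MUST would depart from the published text.

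Three stronger readings are tempting and are not supported:

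- *The planned intervals are wider than the design delivers.* Over-coverage needs balance within strata. The Randomization section says only that "Randomization will be performed according to a prescribed computer-generated schedule"; blocking is not stated. Even with blocking, the complication interval covers 94.3% at a 20-point gap.
- *The Wilson method is wrong for a difference because it is a one-sample interval.* A two-sample interval built from Wilson limits exists (Newcombe), so this is a matter of naming.
- *The SDs passed to phase III would be overstated.* A marginal SD is the right input for an unadjusted comparison and a cautious one for an adjusted comparison.

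**Conclusion.** The point holds as a modest, free improvement. The design stratifies on MUST, and no stated between-group estimate uses it. If MUST predicts outcome, the planned complication interval is about 2% wider than necessary at a 20-point gap between strata and about 5% at a 30-point gap, assuming 50% complications overall and equal strata. The CCI gain is about 2% to 8% at assumed correlations of 0.2 to 0.4. QoL gains least, because baseline is already in the model. There is no gain if MUST is not prognostic.

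A reader might infer that the inference is invalid or that the go/no-go outcome is at risk. Neither follows: the loss is conservative, is confined to secondary estimates, and cannot affect the proportion of eligible patients randomized.

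**What to change.** In Statistical Analysis:

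- Estimate the complication risk difference stratified by MUST risk, with Mantel-Haenszel weights and a stratified Newcombe (Wilson-based) 95% CI.
- Estimate the CCI mean difference from a linear model with treatment and MUST stratum.
- Add MUST stratum beside baseline score in the QoL models.
- Continue to report unadjusted complication rates and SDs by group, so that phase III can be planned for either type of analysis.

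The cost is wording only. The stratum is determined for every patient before randomization, so no further data or patients are needed. If MUST turns out not to be prognostic, the penalty is negligible: at most about 0.5% in width in the simulation (0.800 against 0.796).
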